## Methods/Design

### Study design

We will perform a prospective multicenter cohort study in the south of The Netherlands; four regional hospitals will participate in the study (Laurentius hospital Roermond, Orbis medical center Sittard, St. Jans hospital Weert and VieCuri Venlo) together with a tertiary referral center (Maastricht University Medical Centre +). In total, 270 patients will be included within a timeframe of two years. The study will end once the last patient’s final diagnosis based on histology is known.

### Study population

Female patients 18 years of age or older are eligible to participate in the study if they are diagnosed in one of the participating centers with at least one pelvic mass that is suspected to be of ovarian origin, and are to undergo surgery in order to obtain a final histological diagnosis. Exclusion criteria are as follows: pregnancy, age under 18 years, a prior bilateral oophorectomy, insufficient or missing data, no informed consent, surgery did not take place or takes place more than 120 days after RMI and simple ultrasound-based rules are performed, and/or the patient is not able or willing to travel to the center hospital for additional diagnostic procedures.

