### Study procedures

Both RMI and simple rules will be performed in the regional hospitals and center hospital by general gynecologists during the same ultrasound scan. For collection of these variables a routine transvaginal ultrasound is sufficient. Transabdominal ultrasonography will be added if the mass is too large to be seen entirely by using only transvaginal ultrasonography. Gray scale and color Doppler ultrasound live images will be used to obtain all morphologic and blood flow variables to characterize each mass by RMI and by simple rules. The ultrasound will be performed by a general gynecologist or a trainee supervised by a general gynecologist. The sonographer will not be blinded for the serum CA125 level since this is needed to calculate the RMI.

Only when the simple rules are inconclusive the patient will be referred to the center hospital for the second stage tests; i.e., subjective assessment and MRI. From previous publications it can be deducted that this will be in approximately 20 % of patients.

Subjective assessment will be performed by an expert ultrasound examiner. The ultrasound examiner will be a level III sonographer according to the guidelines of the European Federation of Societies for Ultrasound in Medicine and Biology (EFSUMB-criteria), based on -among others- the years of experience, the hours of training and the total number of ultrasound scans performed by the operator [20].

The MRI will be performed at 1.5 Tesla (Intera; Philips Medical Systems, Best, The Netherlands). Conventional 2D T2-weighted sequences in three planes (sagittal, coronal, axial) and 3D T1-weighted sequences in the axial plane will be supplemented with diffusion weighted sequences. The MRI scans will be examined by 2 independent radiologists with experience in MRI, and who are blinded to the outcome of the subjective assessment. Furthermore, a blood sample will be taken for translational research purposes from patients with a mass that cannot be classified by simple rules. These serum samples will be stored for future biomarker studies.

A secured online Case Report Form (CRF) and database (‘MACRO’) are created in which the demographic data, ultrasound data and MRI data will be stored.

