### Management of the mass

The RMI is currently considered the standard diagnostic procedure. Therefore, in case of an RMI outcome of less than 200 – i.e., when a malignancy is not suspected- the mass is currently managed conservatively or with laparoscopy. In case of an RMI outcome of 200 or more the patient is managed together with a gynecological oncologist from the center hospital for comprehensive surgical staging and cytoreductive (debulking) surgery, according to prevailing guidelines.

However, it can be foreseen that conflicting results can occur between the RMI and the simple rules combined with the second stage test. If this is the case an individual risk assessment will be made and all conflicting results will be discussed with the patient, after which a gynecological oncologist will be consulted when deemed necessary. Although the RMI currently is considered standard care, we believe that conflicting results cannot be ignored.

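### Exclusions that can arise only after the index tests leave accuracy in pathway completers, with biases on the comparison that can run in opposite directions

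*Protocol article*

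**What the plan says.** The Study population section of the protocol article gives one list of exclusion criteria. Beside pregnancy, age and prior oophorectomy it names "insufficient or missing data, no informed consent", then "surgery did not take place or takes place more than 120 days after RMI and simple ultrasound-based rules are performed", and finally that "the patient is not able or willing to travel to the center hospital for additional diagnostic procedures". The same section restricts entry to women who "are to undergo surgery in order to obtain a final histological diagnosis".

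Study procedures fixes who needs the second step: "Only when the simple rules are inconclusive the patient will be referred to the center hospital for the second stage tests". It expects that "this will be in approximately 20 % of patients". RMI and the simple rules are both scored at the same first scan.

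Management of the mass says that at an RMI below 200 "the mass is currently managed conservatively or with laparoscopy".

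The Discussion presents the study as the first to test the simple rules as triage within a regional referral structure, and expects it may change guidelines.

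**The concern.** Two of these exclusions cannot be judged at entry. Missing data become known only once the tests should have been done, and the surgery criterion is timed from the tests themselves. A woman whose simple rules are inconclusive and who does not complete the second step has no two-step result, so she falls under missing data even if she agreed to travel at consent. Only inconclusive women need that step, so this removal is confined to women in whom the triage has not produced an answer. RMI has one, because it needs no second visit.

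The surgery criterion raises a separate problem. If planned surgery is dropped more often after a low RMI, the women lost are mainly RMI-negative, and their disease status is never verified.

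Followed as written, the rule yields accuracy among women who completed the pathway and have histology. The claim in the Discussion concerns a referral strategy, in which an uncompleted referral is part of how the strategy performs.

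**Working it through.** **Inputs from the article.** Inconclusive share about 20% (Study procedures). RMI sensitivity 79%, two-step sensitivity 91%, discordant proportions 16% and 4%, 97 malignancies, prevalence 40%, totals 243 and 270 (Sample size calculation). Simple rules where applicable: sensitivity 95%, specificity 91%. Subjective assessment in inconclusive cases: 91% and 93% (Background).

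**Inputs assumed.** The 20% inconclusive share also holds among malignancies. A fraction f of inconclusive women does not attend. A fraction v of RMI-negative women has timely surgery. Neither f nor v is in the article.

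**1. The plan's own figure.** With ψ = 0.16/0.20 = 0.8, the conditional McNemar formula gives discordant pairs m = (1.96/2 + 0.8416 × √(0.8 × 0.2))² / (0.8 − 0.5)² = 19.26. Then 19.26/0.20 = 96.3, so 97; 97/0.40 = 242.5, so 243; 243/0.90 = 270. The stated numbers reproduce and are not in dispute.

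**2. Women affected by a missing second step.** 0.20 × 270 = 54.

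**3. Sensitivity if non-attenders count as not detected.** Take 91% as the value in completers. Sensitivity = 0.91 × (1 − 0.20f). The gain is measured against RMI held at 79%.

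| f | Two-step sensitivity | Gain over RMI |
|---|---|---|
| 0 | 91.0% | 12.0 points |
| 0.1 | 89.2% | 10.2 points |
| 0.2 | 87.4% | 8.4 points |
| 0.3 | 85.5% | 6.5 points |

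**4. The same check with the article's component accuracies, at f = 0.2.** The share of women without a second step is 0.20 × 0.2 = 0.04.

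- Detected at either step: 0.80 × 0.95 + 0.16 × 0.91 = 0.9056. Correctly cleared at either step: 0.80 × 0.91 + 0.16 × 0.93 = 0.8768.
- Excluded: sensitivity 0.9056/0.96 = 94.3%, specificity 0.8768/0.96 = 91.3%.
- Counted as test negative: sensitivity 90.6%, specificity 0.8768 + 0.04 = 91.7%.
- Counted as test positive: sensitivity 0.9056 + 0.04 = 94.6%, specificity 87.7%.

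Under either rule one of the two measures is about 3.6 to 3.8 points lower than with exclusion, and the other changes by less than half a point.

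**5. Loss of surgery after a low RMI.** If the 16% and 4% are the discordant proportions between the two tests among malignancies, the cells are: two-step only 0.16; RMI only 0.04; both positive 0.79 − 0.04 = 0.75; neither 0.05. If all RMI-positive women and a fraction v of RMI-negative women are operated on, the verified total is T = 0.79 + 0.21v. Apparent RMI sensitivity is 0.79/T, two-step sensitivity (0.75 + 0.16v)/T, and the gain (0.16v − 0.04)/T.

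| v | RMI | Two-step | Gain |
|---|---|---|---|
| 1.0 | 79.0% | 91.0% | 12.0 points |
| 0.9 | 80.7% | 91.3% | 10.6 points |
| 0.8 | 82.5% | 91.6% | 9.2 points |

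Both sensitivities are inflated, RMI's by more. If only women negative on both tests go without surgery, the gain is 0.12/(0.95 + 0.05v), which stays at 12.1 points for v = 0.9 or 0.8.

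**The case against.** The strongest reply is that the text does not show result-dependent exclusion for every criterion named, and much of that reply stands.

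- **Travel.** A reader might infer that this criterion is applied only after an inconclusive result. The article does not say so. Consent precedes enrolment (Ethics and dissemination), and willingness asked of everyone at that point would not depend on any test. The gap that remains is the woman who agrees and then does not attend.
- **Missing data.** A reader might take all missing data to depend on the test results. Nothing supports that. The dependence is clear only when the missing item is the second step.
- **No surgery.** A reader might conclude that conservatively managed women are systematically removed. Eligibility already requires planned surgery, so most such women lie outside the target population by design. What remains is planned surgery that was cancelled or delayed. Excluding women without a reference standard is a normal limit of a histology-verified study. Management of the mass also provides for an individual decision when the tests conflict, so RMI alone need not determine surgery.
- **Direction.** A reader might suppose that every exclusion flatters the triage. The working shows otherwise: RMI-driven loss of surgery shrinks the difference.
- **Scoring.** Counting a non-attender as missed if malignant and as not cleared if benign gives one event two opposite results according to histology. That is a worst-case bound, not a rule a clinic could apply, and it should not be the primary analysis.

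The reply does not remove the core. The listed exclusions include events that can occur only after testing, and an analysis plan that is not shown cannot be presumed to restore women whom the protocol defines as excluded.

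**Conclusion.** The point holds in a limited form. Excluding women for an absent second step removes only cases in which the triage gave no answer while RMI did, and this favours the two-step test relative to counting them as failures. On the plan's 91%, sensitivity would be 89.2, 87.4 or 85.5% at 10, 20 or 30% non-attendance. This assumes a 20% inconclusive share among malignancies and an unchanged RMI sensitivity of 79%. Loss of planned surgery that is more likely after a low RMI acts against the triage: the apparent gain falls from 12.0 to 10.6 or 9.2 points if 90% or 80% of RMI-negative women are operated on. Eligibility for planned surgery limits this second route.

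The attendance and surgery rates are assumptions, so these figures are ranges and not estimates of actual bias. The documents do not support a claim that the comparison is biased in one known direction. The net effect cannot be judged unless the exclusions are reported by test result.

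**What to change.** - Apply the travel criterion only at consent, to all women and before any index test, and say so.
- Do not exclude an enrolled woman who has histology, an RMI and a simple-rules result merely because the second step is missing. Keep the completers estimate. Add a pre-specified sensitivity analysis that counts an inconclusive result without a second step as test positive and then as test negative, by the same rule in malignant and benign women.
- Tabulate women without surgery within 120 days by RMI result and triage result, and add a verification-bias sensitivity analysis (for example Begg-Greenes, or best and worst case).
- Women who lack the data to compute RMI or the simple rules may still be excluded.

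The cost is a wording change to the eligibility criteria and a modest amount of extra analysis. RMI and the simple rules come from the first scan, so no new procedure is needed. The downside is that triage accuracy may look somewhat lower.

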### Study parameters

The primary research question is the comparison of diagnostic test accuracy between the currently used RMI and a new two-step triage system for the correct differentiation between malignant and benign adnexal masses. Main study parameters are sensitivity, specificity, positive predictive value, negative predictive value and positive and negative likelihood ratios. Sensitivity is defined as the percentage of women with ovarian cancer diagnosed with a malignancy by the RMI and the two-step test, respectively. The positive predictive value is defined as the percentage of patients with a positive test result having malignant disease. The final diagnosis will be based on histology (gold standard).

Based on the results, a cost-effectiveness analysis will be performed.

### Study procedures

Both RMI and simple rules will be performed in the regional hospitals and center hospital by general gynecologists during the same ultrasound scan. For collection of these variables a routine transvaginal ultrasound is sufficient. Transabdominal ultrasonography will be added if the mass is too large to be seen entirely by using only transvaginal ultrasonography. Gray scale and color Doppler ultrasound live images will be used to obtain all morphologic and blood flow variables to characterize each mass by RMI and by simple rules. The ultrasound will be performed by a general gynecologist or a trainee supervised by a general gynecologist. The sonographer will not be blinded for the serum CA125 level since this is needed to calculate the RMI.

Only when the simple rules are inconclusive the patient will be referred to the center hospital for the second stage tests; i.e., subjective assessment and MRI. From previous publications it can be deducted that this will be in approximately 20 % of patients.

Subjective assessment will be performed by an expert ultrasound examiner. The ultrasound examiner will be a level III sonographer according to the guidelines of the European Federation of Societies for Ultrasound in Medicine and Biology (EFSUMB-criteria), based on -among others- the years of experience, the hours of training and the total number of ultrasound scans performed by the operator [20].

The MRI will be performed at 1.5 Tesla (Intera; Philips Medical Systems, Best, The Netherlands). Conventional 2D T2-weighted sequences in three planes (sagittal, coronal, axial) and 3D T1-weighted sequences in the axial plane will be supplemented with diffusion weighted sequences. The MRI scans will be examined by 2 independent radiologists with experience in MRI, and who are blinded to the outcome of the subjective assessment. Furthermore, a blood sample will be taken for translational research purposes from patients with a mass that cannot be classified by simple rules. These serum samples will be stored for future biomarker studies.

A secured online Case Report Form (CRF) and database (‘MACRO’) are created in which the demographic data, ultrasound data and MRI data will be stored.

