## Background

Ovarian cancer is the second most common gynecologic malignancy [1]. In 2008 it was the seventh leading cause of cancer deaths in women worldwide [1, 2]. Estimating the risk of malignancy is essential in the management of adnexal masses. Patients with a malignancy should undergo an appropriate staging procedure or debulking surgery carried out in specialized surgical centers. This is associated with a better median survival [3]. Vice versa, patients with a benign lesion may be managed conservatively or with minimal invasive surgery in non-specialized hospitals. This will limit morbidity and avoid unnecessary costs: laparoscopic surgery is associated with less blood loss, shorter hospital stay, and fewer postoperative complications with an improved quality of life and faster return to preoperative functioning [4].

There are several methods to distinguish benign from malignant adnexal masses. The commonly most used method in clinical practice is the Risk of Malignancy Index (RMI) [5–7]. The RMI is an easy to use scoring system that is recommended by many national guidelines in the differential diagnosis of ovarian masses. The RMI combines ultrasound variables, menopausal status and serum CA125 into a score used to predict the risk of ovarian cancer before surgery (Fig. 1). The reported sensitivity and specificity of RMI at a cut-off value of 200 are 75–80 % and 85–90 %, respectively [8]. This results in an incorrect diagnosis (false positive or false negative) in one out of five women with an adnexal mass. These patients therefore receive inappropriate treatment, potentially leading to increased morbidity and/or mortality.

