**Fig. 1 Fig1:**
[figure not shown]
Schematic presentation of three different RMI score algorithms. This figure illustrates 3 different versions of the RMI score system: RMI-I [5], RMI-II [6] and RMI-III [7]. These versions differ from each other in the score attributed to the ultrasound features and menopausal status of the patient

The ‘simple ultrasound-based rules’ (simple rules) is another method to differentiate between benignity and malignancy. This method uses different morphological ultrasound features of adnexal masses (without including menopausal status or serum CA125 measurement). It includes 10 rules (Table 1); five rules to predict malignancy (M-rules) and five rules to predict a benign tumor (B-rules). If both or none of the M- and B-rules are met the test is inconclusive [9,10]. Simple rules are applicable in approximately 80 % of patients with an ovarian mass and in these cases a sensitivity of 95 % and a specificity of 91 % is achieved in previous studies [11].

**Table 1 Tab1:** Benign and malignant ultrasonic features used in simple ultrasound-based rules as proposed by Timmerman et al. [9]

10 Simple ultrasound-based rules	
B-features (for predicting a benign tumor)	
B1	Unilocular
B2	Presence of solid components, of which largest solid component has largest diameter <7 mm
B3	Presence of acoustic shadows
B4	Smooth multilocular tumor with largest diameter <100 mm
B5	No blood flow (color score 1)
M-features (for predicting a malignant tumor)	
M1	Irregular solid tumor
M2	Presence of ascites
M3	At least four papillary structures
M4	Irregular multilocular solid tumor with largest diameter ≥100 mm
M5	Very strong blood flow (color score 4)

*Rule 1*: If ≥ 1 M-features are present in absence of B-feature(s), the mass is classified as malignant

*Rule 2*: If ≥ 1 B-features are present in absence of M-feature(s), the mass is classified as benign

*Rule 3*: If both M-features and B-features are present, or if no B- or M-features are present, the result is inconclusive and a second stage test is recommended

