### Analysis

#### Sample size calculation

The RMI has a relatively low sensitivity (75–80 %). By reducing the amount of false negative test results the patient will benefit most in terms of prognosis and survival. For the calculation of the sample size we therefore focused on sensitivity as the most important primary objective.

This study is designed to have an 80 % power to detect an increase of sensitivity from 79 % for the RMI to 91 % for the two-step triage test with a two-sided α value of 0.05. Using a matched pair design, it can be estimated that the total discordance between the preoperative diagnosis and the final diagnosis based on histology, obtained by surgery, is 20 % (16 % and 4 % respectively). Based on McNemar’s test a minimum sample size of 97 women with a malignancy is required [23]. Taking a prevalence of malignancy of 40 % into account, the study will need 243 patients in total. To allow for loss of power of 10 % a total of 270 women will be enrolled in the study.

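### The examiner scores both tests knowing CA125, for a reason that covers only the RMI arithmetic, so the paired comparison can be biased in an unknown direction

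*Protocol article*

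**What the plan says.** All of this is in the protocol article.

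- Study procedures, on who scores what: "Both RMI and simple rules will be performed in the regional hospitals and center hospital by general gynecologists during the same ultrasound scan". The live images "will be used to obtain all morphologic and blood flow variables to characterize each mass by RMI and by simple rules".
- Study procedures, on blinding at that scan: "The sonographer will not be blinded for the serum CA125 level since this is needed to calculate the RMI".
- Background, on the RMI: "The RMI combines ultrasound variables, menopausal status and serum CA125 into a score used to predict the risk of ovarian cancer before surgery". The caption of Fig. 1 adds that the three RMI versions differ in the scores given to ultrasound features and to menopausal status.
- Background, on the simple rules: they rest on ultrasound morphology, "without including menopausal status or serum CA125 measurement". Table 1 lists five benign and five malignant features and the three rules that combine them.
- Statistical analysis: McNemar's test compares the RMI with the two-step test on both sensitivity and specificity.

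**The concern.** The reason given for unblinding does not reach as far as the unblinding does. It explains why CA125 must be available when the RMI is calculated. It does not explain why the examiner should know CA125 while deciding whether a solid tumor is irregular or which color score applies.

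The simple rules are the first step of the triage test, and they are meant to work without CA125. If the value is known while they are scored, the study may evaluate simple rules read with knowledge of CA125, which is not the test that the article defines and hopes to see adopted. The same examiner also scores the RMI ultrasound items, so those are exposed as well. At stake is the primary comparison: each woman contributes a pair of results, and McNemar's test depends entirely on the pairs that disagree. Anything that makes one reading lean on information belonging to the other test changes how many pairs disagree, and in which direction.

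**Working it through.** **1. Is CA125 needed at the scan?** Set side by side, the Background names ultrasound variables, menopausal status and CA125 as separate ingredients of the RMI, and Study procedures uses the scan to collect morphology and blood flow. The RMI formula itself is in a figure that is not shown, so the separate entry of CA125 is read from the Background text and the figure caption. On that reading, CA125 can be added after the ultrasound items are recorded. Nothing in the article says that the simple rules are recorded before CA125 is seen.

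**2. How could knowledge of CA125 change a result?** Some features in Table 1 leave room for judgement (irregularity, color score). Others are size limits or presence/absence and leave less. By the rules under Table 1:

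- an M-feature added to a mass with no features turns inconclusive into malignant;
- an M-feature added to a mass with only B-features turns benign into inconclusive and sends the woman to the second stage;
- a low CA125 can work the other way, towards leaving out an M-feature or adding a B-feature.

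Both the classification and the route to the second stage can therefore move.

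**3. The plan's own figures.** Inputs from Sample size calculation: "This study is designed to have an 80 % power", "with a two-sided α value of 0.05", sensitivity 79 % v 91 %, discordance 20 % split 16 % and 4 %, prevalence 40 %, allowance 10 %. Since 16 − 4 = 12 = 91 − 79, I read 16 % as malignancies found by triage only and 4 % as those found by the RMI only. With p = 0.16/0.20 = 0.8:

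- discordant pairs = [(1.960/2 + 0.8416 × √(0.8 × 0.2)) / (0.8 − 0.5)]² = (1.3166/0.3)² = 19.26;
- malignancies = 19.26/0.20 = 96.3, so 97;
- total = 97/0.40 = 242.5, so 243; enrolled = 243/0.90 = 270.

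All three figures reproduce. Power at 97 is Φ[(|p − 0.5|√m − 1.960/2)/√(p(1 − p))] with m = 97 × 0.20 = 19.4, which gives 80.3 %.

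**4. Which way could a leak push sensitivity?** The leak sizes below are assumptions; the documents give none. Let knowledge of CA125 turn some discordant malignant cases into agreement with the RMI, with the RMI held at 79 %.

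| Assumed change | Triage only / RMI only | Difference (points) | Power at 97 |
|---|---|---|---|
| none | 16 % / 4 % | 12 | 80.3 % |
| RMI-only cell loses 25 % | 16 % / 3 % | 13 | 91.0 % |
| RMI-only cell loses 50 % | 16 % / 2 % | 14 | 98.0 % |
| both cells lose 25 % | 12 % / 3 % | 9 | 65.9 % |
| both cells lose 50 % | 8 % / 2 % | 6 | 45.5 % |
| triage-only cell loses 25 % | 12 % / 4 % | 8 | 50.5 % |

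One line in full: for 12 %/3 %, p = 0.8 and m = 97 × 0.15 = 14.55, so (0.3 × 3.814 − 0.980)/0.4 = 0.411 and Φ(0.411) = 0.659. An unconditional power formula gives 76 % with no leak and 63 % and 46 % for the two even pulls, so the direction does not depend on the formula.

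**5. If the tests were truly equal.** Assume 10 %/10 % discordance and a one-way leak that removes k points from the RMI-only cell. With d = k, ψ = 0.20 − k and n = 97, the rejection probability is Φ[(d√n − 1.96√ψ)/√(ψ − d²)] + Φ[(−d√n − 1.96√ψ)/√(ψ − d²)]. It is 5 % at k = 0, 7.5 % at 2 points and 24.4 % at 5 points (about 2 and 5 women of 97). This is the unfavourable one-way case, not a forecast.

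**The case against.** The strongest defence has three parts.

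First, the unblinding is openly stated and may mirror practice: the RMI is standard care, and the study sets out to test triage within a geographic referral system, where examiners may well know CA125. As an estimate of performance in use, that is defensible. But it is not the reason the article gives, and it would still need to be stated and its effect reported as a limitation.

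Second, the article does not show that CA125 sways any feature, and several of the ten are size limits or presence/absence. This stands as a limit on the size of the concern. It does not remove the concern, because features that need judgement remain and a single feature can change the result.

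Third, a reader might infer that the leak must favour triage, because only the triage test can gain information that it is not meant to have. The documents do not support that. The same unblinded examiner scores the RMI items; an even pull towards the RMI under the 16/4 split works against triage; a low CA125 can remove detections made by triage alone; and a high CA125 in a benign mass can lower triage specificity, which is also tested.

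A reader might also extend the criticism to the second stage, since the MRI readers are those "who are blinded to the outcome of the subjective assessment" and no masking of the expert examiner is described. That rests on silence in a condensed article, which also does not say what information travels with the referral. It is not part of this point.

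**Conclusion.** The concern holds in limited form. The stated reason justifies having CA125 for the RMI calculation, not knowing it while ultrasound features are scored. As written, the two tests are not read independently, and the paired comparison of sensitivity and specificity can be biased towards triage or towards no difference.

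The size cannot be derived. The table shows only that plausible patterns run both ways, with differences from 6 to 14 points against a planned 12. Those values rest on assumed leak rates, an RMI sensitivity unaffected by the leak, and the reading of 16 % and 4 % given above. They should not be quoted as an estimate, and no share of the planned gain can be attributed to knowledge of CA125.

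The planned numbers (97, 243, 270) are not in question. The change should be made because one direction threatens the validity of a positive result, the other costs power, and the remedy is cheap.

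**What to change.** - Have the examiner record and lock the ten simple-rule features and the RMI ultrasound items in the online CRF before CA125 is opened. Compute the RMI afterwards, in the database or centrally. The article lists demographic, ultrasound and MRI data in the database but not CA125, so a field may have to be added.
- Add one yes/no item: was CA125 already known to the examiner at the scan?
- Keep all women in the primary analysis, and report a sensitivity analysis without those whose CA125 was already known.
- Reword the blinding sentence in Study procedures to match. If unblinding is kept because it reflects practice, give that as the reason and report non-independent reading as a limitation.

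The cost is a CRF field order and lock, one or two fields, and revised wording. No staff, tests, visits or patients are added; clinical management is untouched, because CA125 is available as soon as the items are locked. There are two downsides: masking is incomplete where CA125 was known before the scan, and the sensitivity analysis loses precision by an amount that depends on how many women that is.
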